# “FIND Technology”: investigating the feasibility, efficacy and safety of controller-free interactive digital rehabilitation technology in an inpatient stroke population: study protocol for a randomized controlled trial

**DOI:** 10.1186/s13063-016-1318-0

**Published:** 2016-04-16

**Keywords:** Rehabilitation, Exergames, Exercise, Activity

## Abstract

**Background:**

Stroke results in significant disability, which can be reduced by physical rehabilitation. High levels of repetition and activity are required in rehabilitation, but patients are typically sedentary. Using clinically relevant and fun computer games may be one way to achieve increased activity in rehabilitation.

**Methods/design:**

A single-blind randomized controlled trial will be conducted to evaluate the feasibility, efficacy and safety of novel stroke-specific rehabilitation software. This software uses controller-free client interaction and inertial motion sensors. Elements of feasibility include recruitment into the trial, ongoing participation (adherence and dropout), perceived benefit, enjoyment and ease of use of the games. Efficacy will be determined by measuring activity and using upper-limb tasks as well as measures of balance and mobility. The hypothesis that the intervention group will have increased levels of physical activity within rehabilitation and improved physical outcomes compared with the control group will be tested.

**Discussion:**

Results from this study will provide a basis for discussion of feasibility of this interactive video technological solution in an inpatient situation. Differences in activity levels between groups will be the primary measure of efficacy. It will also provide data on measures of upper-limb function, balance and mobility.

**Trial registration:**

ACTRN12614000427673. Prospectively registered 17 April 2014.

## Background

In the US alone, one person per minute has a stroke, and although death rates have declined over the last decade, the burden of disease remains high [13]. Physical rehabilitation has the potential to positively impact functional outcomes and improve this burden; however, this requires a high dose of therapy. A significant factor limiting rehabilitation outcomes is low levels of patient activity [10]. Observational studies in different countries have found that patients after stroke in rehabilitation are surprisingly inactive for the vast majority of the waking day. For example, only 13 % of a stroke unit patient’s day is typically spent in activities related to functional outcome, such as active therapy or walking practice [2]. Many rehabilitation activities, aimed at stimulating neuroplasticity, are by their very nature repetitive and tend to be tedious [19]. One method by which engagement with rehabilitation programs and levels of activity could be improved involves the use of fun and engaging video games.

Commercial, off-the-shelf devices such as the Microsoft Xbox Kinect (Microsoft Corporation, Redmond, WA, USA) are relatively inexpensive and use motion capture and feedback technologies with potential for use in rehabilitation. Interactive video games increase adherence to and enjoyment of exercise in the general population [1] and have the potential to increase the dose of repetitive exercise completed by people with reduced mobility. Exercise-based video games could be used to increase exercise dose during therapy and to enable exercise outside of therapy hours. This is true both in inpatient and outpatient rehabilitation settings as well as at home after discharge from hospital.

In particular, the Kinect for Xbox 360, or simply Kinect, is a “controller-free gaming and entertainment experience” by Microsoft for the Xbox 360 video-game platform and is now also supported by PCs via Windows 8. It enables users to control and interact with the Xbox 360 without the need to touch a game controller, through a user interface using gestures and spoken commands. Kinect enables full-body depth-based three-dimensional motion-capture, facial recognition and voice recognition capabilities. This differentiates it from previous generations of interactive technologies that have been used in rehabilitation.

Despite the promise of such low-cost, consumer-based technologies, many, if not all, off-the-shelf video-game solutions are inappropriate for individuals with functional impairment [16]. There is an opportunity for purpose-built, clinically relevant video game-based rehabilitation to add significant value to current rehabilitation practice. Jintronix, a Montreal-based company, has recently launched a Kinect-based rehabilitation system, Jintronix Rehabilitation System (JRS), which provides an easy-to-use software solution (JRS WAVE) for patients to use. The software solution has been designed in collaboration with physical and occupational therapists and draws upon the motor relearning recommendations by Carr and Shepard [5]. As such, upper limb, sitting balance, standing balance and stepping rehabilitation tasks have been programmed in the JRS WAVE as fun and engaging video games that can be played at a number of different levels of complexity and speed. The system is also capable of automatically measuring changes in the range, speed and quality of motion to give patients instant feedback on their progress.

A second feature of the JRS WAVE is a cloud-based client management telehealth system for clinicians to recommend rehabilitation tasks and track and record performance of those tasks (JRS PORTAL). The PORTAL allows clinicians to provide patients regular updates and information on what has happened to them with daily, weekly or monthly progress reports on their rehabilitation, either face-to-face or remotely.

The proposed project will evaluate the feasibility, efficacy and safety of the JRS WAVE for use in an Australian stroke inpatient rehabilitation context. Elements of feasibility include recruitment into the trial, ongoing participation (adherence and dropout), perceived benefit, and enjoyment and ease of use of the games. Efficacy will be determined by measuring physical activity (using an accelerometer) and using upper-limb tasks as well as measuring changes in balance and mobility over time between the two groups. Adverse events will be monitored and changes in pain and fatigue with the interventions will be used to determine safety of the system. We will test the hypothesis that the intervention group will have increased levels of physical activity within rehabilitation and improved physical outcomes compared with the control group.

## Methods/Design

A single-blind randomized controlled trial will be conducted on two rehabilitation wards of a secondary referral hospital. Participants will be randomly assigned into the JRS WAVE intervention that will last for the duration of the stay on the ward, with a minimum dose of 8 days and maximum of 40 or usual care. All participants will provide written informed consent, and ethical clearance has been received.

### Participants

#### Inclusion

Eligible participants will be adults admitted to the two rehabilitation wards at the Launceston General Hospital with reduced mobility after haemorrhagic or infarct cerebrovascular accident of recent onset (less than 6 months) with a clinician-assessed capacity for improvement in mobility.

Exclusion criteria will be the following: a marked cognitive impairment so that instructions are not able to be carried out (determined by the therapist); insufficient English language skills to participate in rehabilitation and no available interpreter; a medical condition precluding exercise (unstable cardiac disease, uncontrolled hypertension, uncontrolled metabolic diseases, large abdominal aortic aneurysm or a weight-bearing restriction); or severe receptive or expressive dysphasia of severe visual impairment.

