#### Recruitment

All patients admitted to the two rehabilitation wards during the trial period will be screened for inclusion by a senior neurological physiotherapist. Eligible patients will be given information about the project and if they are interested, a research assistant (physiotherapist) will be contacted to provide further information. Written consent will be obtained before participation in the project. Demographic and background information will be collected. Ethical approval for this study has been received from the Human Research Ethics Committee (Tasmania) Network (approval number H0013769).

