#### Randomization

Allocation into intervention or control group will be performed by using a computer-generated random number schedule with variable block sizes 2–6. Generation of the randomization sequence will be generated by a researcher not involved in recruitment or assessment. Group allocation will be concealed by using consecutively numbered opaque sealed envelopes, opened in the presence of the participant after completion of assessment.

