### Data analysis

Data collected during the trial will allow us to describe the participants’ changes in upper-limb function, balance and mobility by using *t* tests or Mann–Whitney *U* tests to compare normally and non-normally distributed data, respectively. Repeated measures analysis of variance will be used to compare changes in the outcome measures over time and between groups (intervention versus control). The level of significance will be set at 0.05.

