## Discussion

The proposed project will discuss the feasibility and efficacy of the JRS WAVE. Uptake from screening to recruitment, adherence to the intervention and rates of dropout will be discussed. Feedback from clinicians in terms of system utility will be explored. Feedback from clients on the perceived benefits of this type of rehabilitation and enjoyment and ease of use of the games will also be discussed. Changes in pain and fatigue within each session and between the intervention and control groups will be analysed. Differences in activity levels during the two different interventions (JRS WAVE versus group exercise) will be investigated. Between-group differences for outcome measures of upper-limb function as well as balance and mobility will be investigated.

The primary outcome of efficacy consists of the differences in activity levels from using video technology in rehabilitation compared with usual rehabilitation. It will also provide data for new controller- and device-free motion capture software on measures of upper-limb function, balance and mobility. Much of the published research reviewing the effectiveness of interactive technology games with commercial devices has not used motion capture software in a controller-free situation. For example, the wii™ system for balance requires standing on a platform and the upper-limb tasks require the client to hold (or have strapped to their hand if they do not have grasp capacity) a device that the sensor recognises [6].

This software has been iteratively designed with feedback from the clinicians to form a system that meets the needs of stroke clients in the acute hospital setting as they begin their rehabilitation pathway. This system is vastly configurable, giving the clinicians the ability to tailor the program and modify it in an ongoing way to meet the needs of the clients. The different levels of disability of the clients enrolled will provide challenges when determining between-group differences.

Strengths of this study include that it collects feasibility data from both clients and clinicians. It is a well-powered study with an active control group to allow comparisons across a range of functional measures. Also, both groups are matched for time in rehabilitation (rather than the intervention as additional therapy) and this will allow direct comparison of the groups.

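### Time since stroke, which the entry rule requires to be known, is used in neither the allocation nor the stated comparison, so a modest and nearly free gain in precision on the functional outcomes is left untaken

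*Protocol article*

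**What the plan says.** The Inclusion section recruits "adults admitted to the two rehabilitation wards" with reduced mobility after a "cerebrovascular accident of recent onset (less than 6 months" and a clinician's judgement that mobility can improve. Six months is an upper limit, and no minimum time from onset is given.

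Allocation uses a "computer-generated random number schedule with variable block sizes 2–6". No stratification factor is named.

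Under Data analysis, upper-limb function, balance and mobility are described "by using *t* tests or Mann–Whitney *U* tests to compare normally and non-normally distributed data, respectively". In addition, "Repeated measures analysis of variance will be used to compare changes in the outcome measures over time and between groups". Group and time are the only factors mentioned.

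On baseline data, the Recruitment section says only that "Demographic and background information will be collected". Apart from the entry rule, time since stroke does not appear in the article.

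**The concern.** The functional part of the efficacy question concerns change in balance, mobility and arm function between pre-test and post-test, which is at 8 weeks or at discharge if earlier. A patient soon after stroke and one several months after may improve by different amounts over the same stay, whatever group they are in. The pre-test score captures where each patient starts. It need not capture how fast each is recovering, so two patients with equal pre-test reach may differ in expected post-test reach.

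If so, part of the between-patient variation in outcome could be predicted before randomization. An analysis that ignores it carries that part in the error term. What is at stake is precision, in a trial of 63 to 74 patients that has little to spare.

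**Working it through.** **Inputs from the article (Sample size and justification).** Functional reach SD 7.4 cm at baseline; target difference 3.7 cm; significance level 0.05 (taken as two-sided); power 80%; sample size 63; 74 recruited to allow for 15% dropout.

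**Input assumed.** r, the partial correlation between time since stroke and post-test score given pre-test score. The article gives no value. The range shown is 0.1 to 0.5.

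**Step 1: the plan's own figure.** The number per arm is 2 × (1.960 + 0.842)² × (7.4/3.7)² = 2 × 7.85 × 4 = 62.8, so 63 per arm and 126 in total. The article's 63 matches the per-arm number but is used as the trial total. Its dropout step agrees with that use: 63/0.85 = 74.1. With 63 analysed in total, power is about 51%; with 74 it is about 58%. This is a separate and larger issue. It matters here because it shows how little precision there is.

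**Step 2: standard error without adjustment.** With 63 analysed in two equal arms, SE = 7.4 × √(4/63) = 7.4 × 0.252 = 1.86 cm. The 95% half-width is 1.96 × 1.865 = 3.65 cm.

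**Step 3: effect of adjusting for time since stroke.** Residual variance is multiplied by 1 − r², and the interval width by √(1 − r²). The equivalent gain in patients is 1/(1 − r²) − 1. Power is approximately Φ(3.7/SE − 1.96).

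| Assumed r | Variance removed | Interval narrower by | Equivalent extra patients | 95% half-width, cm (63 analysed) | Power (63 analysed) |
|---|---|---|---|---|---|
| 0 | 0% | 0% | 0% | 3.65 | 51.0% |
| 0.1 | 1% | 0.5% | 1% | 3.64 | 51.4% |
| 0.2 | 4% | 2.0% | 4% | 3.58 | 52.6% |
| 0.3 | 9% | 4.6% | 10% | 3.49 | 54.8% |
| 0.4 | 16% | 8.3% | 19% | 3.35 | 58.1% |
| 0.5 | 25% | 13.4% | 33% | 3.17 | 63.0% |

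**Step 4: how far the centimetre figures can be trusted.** Because r is defined after allowing for pre-test, it should act on the residual SD given pre-test, not on the raw baseline SD of 7.4 cm. The article gives no pre/post correlation. If it were 0.6 to 0.7, the residual SD would be 7.4 × √(1 − 0.36) = 5.9 cm to 7.4 × √(1 − 0.49) = 5.3 cm. At r = 0.3 the half-width would then fall from 2.92 to 2.79 cm, or from 2.61 to 2.49 cm. The percentages in columns 2 to 4 are the same whichever SD is used; the last two columns are not.

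**Step 5: chance imbalance.** The between-arm difference in any standardised baseline variable has a standard error of √(4/63) = 0.252 SD. At r = 0.3 and SD 7.4 cm this moves the estimated effect by 0.3 × 0.252 × 7.4 = 0.56 cm (one standard error), or ±1.10 cm at 95%. With a residual SD of 5.9 to 5.3 cm the range is about ±0.9 to ±0.8 cm. This is not an extra error: 3.65² − 1.10² = 12.1, and √12.1 = 3.48, which is the adjusted half-width of Step 3 within rounding. The imbalance is the r² share of the ordinary sampling variance, seen from another side.

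**The case against.** The strongest case against is that nothing in the article is wrong: a randomized comparison by t test is valid, and covariate choice is often left to an analysis plan that is not shown. The first half stands. The second stands in part. The article does not exclude covariates, but it does fix a method, that method is unadjusted, and its Mann–Whitney branch cannot take a covariate. The point is therefore a better choice for a stated analysis, not a complaint about silence.

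Several stronger readings are tempting and are not supported:

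- *Chance imbalance in time since stroke could pass for a treatment effect.* Randomization keeps the type I error at its nominal level, and Step 5 shows that the imbalance is already inside the standard error. Only precision is lost.
- *The trial pools patients from days to nearly six months after stroke.* That is the permitted range. Patients must be current inpatients on a rehabilitation ward with capacity to improve, which probably narrows the actual spread. No distribution is given, so neither the spread nor its skewness is known.
- *The Discussion promises an early population that the entry rule contradicts.* The phrase "meets the needs of stroke clients in the acute hospital setting as they begin their rehabilitation pathway" describes what the software was designed for. It does not define who may enter the trial.
- *The primary efficacy result is at risk.* Primary efficacy is activity level, monitored by accelerometer for one week. The argument about recovery rates concerns change in function over the stay and reaches that outcome only weakly.
- *The adjustment is free.* It is cheap, but it has a cost, given with the change proposed below.

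It is also fair to say that nothing in the article shows that time since stroke predicts outcome beyond pre-test score, and that the Discussion singles out level of disability as its worry about heterogeneity. Both points argue for the lower part of the assumed range.

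**Conclusion.** The point holds as a modest improvement in precision for the functional outcomes. The entry window is wide, the variable must be established to apply it, and neither the allocation nor the stated comparison uses it. The comparison remains unbiased with a correct type I error.

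The size depends on a correlation that the article does not give. Over an assumed r of 0.1 to 0.5 the gain is 1% to 25% of residual variance. At 0.3 it is 9% of variance and an interval about 5% narrower, for example 3.65 to 3.49 cm on functional reach if the residual SD were 7.4 cm. On that same SD, power with 63 analysed rises from 51% to about 55% at r = 0.3 and to 63% at r = 0.5. Adjustment for time since stroke thus does not bring the trial to its intended 80% anywhere in that range, and it is no answer to the sample size problem in Step 1.

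**What to change.** Leave eligibility and allocation as they are. For the functional outcomes, replace the unadjusted comparison with a prespecified ANCOVA of the post-test score on group, pre-test score and days from stroke onset to pre-test. Log-transform the days if their distribution proves skewed, a check to be made without reference to group. For outcomes unsuited to a normal model, name a rank-based equivalent that accepts covariates, in place of the Mann–Whitney test. Applying the same covariate to accelerometer activity is optional. Fix the choice before unblinded data are seen.

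The cost is one degree of freedom per covariate, a change of method for the non-normal outcomes, and a recorded onset date. The last is a small addition if sites now record only that the stroke was under 6 months old. No visit, test or clinical procedure changes.

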#### Sample size and justification

Sample size calculation was based on previously reported clinical trial data and based on the outcome measure of functional reach, that provided baseline mean (standard deviation) data of 25.6 (7.4) cm [14]. Researchers determined that a clinically relevant difference of 3.7 cm would require a sample size of 63 (*P* <0.05, power 80 %). Seventy-four participants will be recruited to allow for a 15 % dropout rate. The proposed size of this study is comparable to more recently published trial data, which suggest that a clinical difference of 3 cm would require 78 participants [3].

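### The 63 participants calculated for a 3.7 cm difference in functional reach is a per-group number, but the plan uses it as the two-arm total; an unadjusted comparison then has about 50% power, not 80%

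*Protocol article*

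**What the plan says.** The section Sample size and justification says that the calculation was "based on the outcome measure of functional reach", using "baseline mean (standard deviation) data of 25.6 (7.4) cm". It continues that "a clinically relevant difference of 3.7 cm would require a sample size of 63", at a significance level of 0.05 and 80% power. It does not say whether 63 is per group or in total, or whether the test is one- or two-sided.

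The next sentence sets the recruitment target: "Seventy-four participants will be recruited to allow for a" 15% dropout rate. The section then likens the study's size to other trial data implying 78 participants for a 3 cm difference.

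The design has two arms (Randomization; no allocation ratio is given). Data analysis plans t tests or Mann–Whitney tests, and repeated measures ANOVA for changes over time and between groups, at the 0.05 level. The Discussion lists as a strength: "It is a well-powered study with an active control group to allow comparisons across a range of functional measures".

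**The concern.** A difference of 3.7 cm against an SD of 7.4 cm is a standardised difference of 0.5. For a two-group comparison at two-sided 5% and 80% power, that needs a little over 60 per group. The article arrives at that number but appears to spend it on the whole trial.

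If so, the evaluable sample is half of what the stated power requires. A functional-reach result that missed significance would be read as coming from an 80%-powered comparison, when the trial would have about an even chance of missing the very difference that it calls clinically relevant. The strength claimed in the Discussion would also lack support on the one outcome for which the article gives a calculation.

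**Working it through.** **Inputs.** From Sample size and justification: SD 7.4 cm, difference 3.7 cm, significance level 0.05, power 80%, dropout 15%, 74 recruited. Assumed because the article does not state them: two-sided test and 1:1 allocation.

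**Step 1: reproduce 63.** The normal-approximation formula for two independent means is

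n per group = 2 × (1.960 + 0.842)² × (SD/difference)² = 2 × 7.849 × (7.4/3.7)² = 2 × 7.849 × 4 = 62.8, so 63 per group.

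The t-based calculation gives 63.8, so 64 per group. The totals are 126 and 128.

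**Step 2: reproduce 74.** 63/(1 − 0.15) = 74.1, which matches the stated 74. The dropout allowance was therefore applied to 63 as if it were the total. Doing the same with the correct totals gives 126/0.85 = 148.2 (149 recruited) or 128/0.85 = 150.6 (151 recruited).

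**Step 3: look for another route to 63 in total from the stated inputs.**

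| Reading | Required number |
|---|---|
| Two-sample, two-sided | 63 per group (t: 64); 126 total (t: 128) |
| Two-sample, one-sided | 50 per group (t: 51); 100 total (t: 102) |
| Paired or one-sample t, two-sided | 34 |
| Paired or one-sample t, one-sided | 27 |

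None gives 63 in total.

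**Step 4: power of the plan for 3.7 cm, unadjusted comparison, t test.**

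| Evaluable | Power, two-sided | Difference detectable with 80% power |
|---|---|---|
| 63 (31 and 32) | 49.7% | 5.3 cm (0.717 × 7.4) |
| 74 (37 and 37, no dropout) | 56.4% | 4.9 cm (0.660 × 7.4) |

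A one-sided test with 63 evaluable would have about 62%.

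**Step 5: what pre-post correlation r would make 63 in total sufficient?** The normal formula needs an effective SD of 3.7 × √(63/4)/2.802 = 5.24 cm.

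- ANCOVA on baseline has SD 7.4 × √(1 − r²). Setting this to 5.24 gives r = 0.71; by t test about 0.72.
- A change score, which is the group-by-time test when there are two time points, has SD 7.4 × √(2(1 − r)). Setting this to 5.24 gives r = 0.75; by t test about 0.76.

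**Step 6: power with 63 evaluable across assumed correlations (t test, 3.7 cm, SD 7.4 cm at both time points).**

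| Assumed r | ANCOVA | Change score |
|---|---|---|
| 0.3 | 53% | 38% |
| 0.5 | 62% | 50% |
| 0.7 | 78% | 71% |
| 0.75 | 84% | 79% |

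**Step 7: the comparison with 78 participants.** With SD 7.4 cm, a 3 cm difference needs 2 × 7.849 × (7.4/3)² = 95.5, so 96 per group. A total of 78 would imply an SD of 3 × √(78/4)/2.802 = 4.7 cm. That figure therefore rests on a different SD and does not support 63 in total.

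**The case against.** The best defence is that the trial measures everyone before and after, and that Data analysis plans a repeated measures ANOVA on change. Such an analysis can need far fewer patients than a comparison of post-test scores, and step 5 shows that 63 in total would be about right at a correlation near 0.75 (or near 0.71 with ANCOVA). So a reader who infers that 63 in total is impossible under any analysis goes too far. What can be said is that no reading using only the stated inputs gives it. The article states no correlation and uses the raw baseline SD, and that SD returns 63 per group exactly. A per-group number carried forward as a total is much the likelier explanation.

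The second defence is scope. The Abstract and Discussion make activity level the primary efficacy measure, and functional reach is one of several physical outcomes. This stands: a reader might infer that the trial's main comparison has 50% power, but the article gives no inputs from which power for activity could be computed. It does not rescue the statement, because functional reach is the only basis offered for the sample size and is among the functional measures that the Discussion says the trial is well powered to compare.

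Third, the trial also has feasibility aims. That lessens the practical consequence, but the article also sets out to test a hypothesis of improved physical outcomes at the 0.05 level, so the power statement should be right.

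**Conclusion.** The point holds for functional reach. The stated inputs require 63 to 64 evaluable participants per group, 126 to 128 in total; the plan allows for 63 in total. The stated 80% power is therefore wrong as written, and nothing else in the article repairs it.

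The figure of about 50% (56% without dropout) rests on 1:1 allocation, a two-sided test, an SD of 7.4 cm and no use of the baseline value. Under the planned change-over-time analysis, power depends on the unstated correlation and could be lower or higher, as step 6 shows. The documents do not support extending the 50% to the primary activity outcome, nor relying on any single correlation to claim that baseline adjustment restores 80%.

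**What to change.** In Sample size and justification, label 63 as per group and state what the planned recruitment delivers. For example: for functional reach, 63 per group (64 by t test), 126 to 128 evaluable in total, would be required; with 74 recruited and 63 evaluable, allocated 1:1, an unadjusted two-sided comparison has about 50% power for 3.7 cm and 80% power for about 5.3 cm.

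In the Discussion, delete the description of the study as well powered.

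Optionally, analyse the post-test functional-reach score by ANCOVA on the baseline value, which is already collected. This may recover some power. If it is used to support the sample size, state the correlation assumed and show power at lower values too.

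The cost is rewording two paragraphs and accepting a less favourable power statement. No additional patients or measurements are needed.
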